## Abstract

Women with previous gestational diabetes mellitus (post-GDM) have an increased risk of cardiometabolic diseases including type 2 diabetes (T2D). Current diabetes screening is based on the oral glucose tolerance test without nutritional assessments, even though unhealthy dietary patterns were found to expedite disease progression in women post-GDM. While a healthful dietary pattern reduces T2D risk, limited data support a dietary pattern tailored to the Asian population, especially in the Malaysian context. Metabolomic profiles associated with dietary patterns in this population are also lacking. The proposed study aims to investigate both components of dietary patterns and metabolomic profile, known as nutritype signatures, and their association with T2D in women post-GDM. The comparative cross-sectional study will involve a minimum of 126 Malaysian women post-GDM aged 18–49 years. Dietary patterns will be analysed using principal component analysis. Plasma and urinary metabolites will be quantified using one-dimensional proton nuclear magnetic resonance (^1^H NMR) spectroscopy. The aim of the study is identifying the nutritype signatures associated with T2D. The findings will support the development of early prevention measures against T2D in women post-GDM.

## 1. Introduction

Type 2 diabetes (T2D) has reached epidemic proportions in Asia, with the Western Pacific Region contributing to 38% of T2D cases worldwide [1]. Malaysia is the fifth leading country in the Western Pacific Region with the highest prevalence of T2D [1]. The prevalence of T2D in Malaysia has increased by almost 60% over a 10-year period, partly due to a rising prevalence of overweight and obesity, physical inactivity, and dietary practices that include a low intake of fruits and vegetables and high intake of sugar-sweetened beverages [2].

Women previously diagnosed with gestational diabetes mellitus (post-GDM) had a nearly 10-fold relative risk of T2D compared with those with normoglycemic pregnancies [3]. Hence, early identification and intervention are critical to preventing T2D in this high-risk group. Risk factors of T2D in women post-GDM include high prepregnancy body mass index (BMI), sedentary behaviour, and an unhealthy dietary pattern low in carbohydrates but high in animal protein and fat [4,5,6]. Current recommendations support diabetes screening at 6 weeks postpartum via oral glucose tolerance test (OGTT) and/or HbA1c after GDM [7]. However, diabetes screening conventionally does not include nutritional assessments, even though an unhealthy diet is highly relevant in expediting disease progression in women post-GDM [6].

Regarding dietary patterns, adherence to healthful dietary patterns such as the alternate Mediterranean Diet (aMED) was associated with a lower risk of T2D in women post-GDM [8]. The Mediterranean diet is widely acknowledged as a healthy dietary pattern, characterised by high intakes of vegetables, fruits, nuts, grains, legumes, fish, and olive oil [9]. Malaysian adults consume a diet high in fish and green leafy vegetables, yet simultaneously high in rice, sugar, animal protein, and fat [10,11], showing a dissimilarity with dietary patterns commonly practiced in the Western population. Limited research has been conducted on the association between Malaysian-tailored dietary patterns and T2D risk in women post-GDM.

As the nutritional assessments have shifted the focus on dietary patterns, we need to identify biomarkers of dietary patterns via the metabolomics approach. Metabolomics is a tool to measure the full profiles of low-molecular-weight metabolites in biofluids such as blood plasma and serum and urine [12]. Metabolites that can predict the transition from GDM to T2D at postpartum have been identified in various studies, including branched-chain amino acids (BCAAs), hexoses, fatty acids, sphingomyelins, and carnitines [13,14,15,16,17,18]. Nevertheless, most of these studies were limited to Western populations and did not include Asian ethnic groups.

The application of metabolomic techniques in nutrition research has led to the emerging concept of nutritype [19]. Nutritype refers to the expression of overall dietary intake in metabolites and can be used to classify individuals into a specific dietary pattern based on their metabolomic profile [19]. In other words, dietary patterns are analysed together with metabolomic profiles to identify the nutritype signatures of the study population [19].

While the roles of dietary patterns and metabolomics in determining T2D risk are significant, these two parameters have usually been separately studied. Current evidence on the combination of dietary patterns and metabolomic profile (nutritype signatures) in women post-GDM has been inconclusive, with varying results being reported [14,15,16,17]. All of the four studies only focused on specific components of dietary patterns and their metabolomic markers, such as cooking fat and oil [14], dietary fatty acids [15], glycaemic load [16], and dietary BCAAs [17]. None of the studies observed dietary patterns in their entirety. The scant evidence indicates a gap in the knowledge and a pressing need for further studies on nutritype signatures to capture the exposure to T2D in women post-GDM.

This paper describes the protocol of the Malaysian Nutritype (MyNutritype) study, including the methodology, research workflow, outcome measures, and statistical analysis. The study aims to investigate the association between dietary patterns, metabolomic profile, and T2D in women post-GDM.

## 2. Methods

This section describes the finalised study design, study population characteristics, and research workflow of the proposed study.

### 2.1. Design

This is a comparative cross-sectional study involving women post-GDM, named the Malaysian Nutritype (MyNutritype) study. The primary outcome is the nutritype signatures associated with T2D in Malaysian women post-GDM. The secondary outcomes of the study include the comparisons of anthropometric and clinical measurements, biochemical profile, energy and nutrient intake, and lifestyle practices between the three groups of women post-GDM (NGT, prediabetes, and T2D).

The aims of this study are:(a)To determine dietary patterns associated with T2D and prediabetes;(b)To determine the metabolomic profile associated with T2D and prediabetes using one-dimensional proton nuclear magnetic resonance (^1^H NMR) spectroscopy;(c)To identify nutritype signatures (association between dietary patterns and metabolomic profile);(d)To determine the nutritype signatures associated with T2D in women post-GDM;(e)To compare other parameters in women post-GDM with normal glucose tolerance (NGT), pre-diabetes and T2D, which include:i.Anthropometric and clinical measurements;ii.Biochemical profile;iii.Energy and nutrient intake;iv.Lifestyle practices.

### 2.2. Study Setting

The study will be conducted at two sites: Universiti Putra Malaysia (UPM) and Klinik Kesihatan Seri Kembangan. UPM is a tertiary institution and the overall responsible site for this study. The recruitment site at UPM is the Faculty of Medicine and Health Sciences. Klinik Kesihatan Seri Kembangan is a government health clinic that includes a medical outpatient clinic and a maternal and child health clinic. Both sites are located in the Petaling District of Selangor, Malaysia. ^1^H NMR spectroscopy and metabolomic analysis will be performed at the Institute of Bioscience, UPM.

### 2.3. Study Population

The study will include Malaysian women aged 18–49 years with a previous diagnosis of GDM. Exclusion criteria will be the following: pregnant women, recent hospitalisation within the last 6 weeks, and previously diagnosed medical problems (such as type 1 or type 2 diabetes, cancer, and liver or renal disorders). The sample size will be estimated using the mean difference formula [20]. Based on a study that compared dietary intake and metabolomic profile in NGT, prediabetes and metabolomic profile in women post-GDM in Gothenburg, Sweden [14], considering a 95% confidence level and 80% power, a total of 99 subjects will be needed for the study. To account for nonresponse or refusal to participate, an additional 20% of subjects will be required, leading to a minimum of 126 subjects.

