### 2.4. Recruitment

Women who fit the selection criteria will be invited to join the study. Subjects will then be selected using systematic random sampling. Informed written consent will be obtained at enrolment. Subjects will be briefed on the benefits and potential risks of joining the study.

Subject recruitment commenced in March 2021, and enrollment is expected to continue through October 2022. The research workflow is shown in Figure 1.

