#### 2.5.1. Diagnosis of Type 2 Diabetes and Prediabetes

After an overnight fast of 8–12 h, subjects will undergo a 75 g, 2 h OGTT. Blood and urine samples will be taken for HbA1c, insulin, lipid profile, and metabolomic analysis. Subjects will be grouped into either NGT, prediabetes or T2D based on their OGTT and HbA1c results, as advised by the study endocrinologist. Our diagnostic criteria for T2D and prediabetes are based on the Malaysian Clinical Practice Guidelines [7] (Table 1).

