### 2.7. Statistical Analysis

Statistical analysis will be performed using SPSS statistical software version 25.0 (IBM, Chicago, IL, USA). Data for categorical variables will be reported as number and percentage, while continuous data will be reported as mean ± standard deviation (SD). Data normality will be assessed prior to data analysis. The study will analyse the differences in the demographic characteristics between subjects who agreed to participate in the study versus those who did not agree to participate. Pearson’s correlation coefficient test will be used to determine correlations between continuous variables, the Chi-squared test to determine the association between categorical variables, and one-way analysis of variance (ANOVA) to compare the differences between the three groups. Multivariate linear regressions will determine the association between the metabolomic profile and factor scores of each dietary pattern yielded from PCA. Multinomial logistic regression will determine the factors, and the nutritype signature models associated with T2D. Variables significant at the bivariate level will be entered into the regression model as confounders. Crude and adjusted odds ratios (ORs) with a 95% confidence interval (CI) will be presented. Subgroup analyses will also be performed, such as early versus late postpartum (<1 year versus ≥1 year post-GDM), supplement versus nonsupplement users, and obese versus nonobese subjects. A previous study found different risk factors of T2D at early (<1 year) versus late postpartum (≥1 year) following GDM [4]. In case of missing data, the study will report the number of available data for the variable. We will analyse any differences in the characteristics between reporters versus nonreporters. A *p*-value < 0.05 for all statistical tests will be considered significant.

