## 3. Discussion

The study aims to identify the nutritype signatures associated with T2D in women post-GDM using the ^1^H-NMR-based metabolomics approach. Cross-sectional studies in Malaysia found the that the prevalence of T2D in women post-GDM ranges between 0.8% and 6 weeks to 35.5% at 15 years postpartum [44,45,46]. This indicates that regardless of the year of diagnosis, having a previous diagnosis of GDM significantly increases future T2D risk.

Metabolomics has emerged as a crucial tool in discovering dietary biomarkers. Alterations in the metabolome are also implicated in disease development, as they respond to nutrients, disease and stress [19]. Traditional methods for assessing dietary intake, including FFQ, may be prone to bias, recall errors, and underreporting [47]. Dietary biomarkers, on the other hand, provide a more objective and accurate measure of food intake [47]. Together, the use of traditional dietary assessment and metabolomic profiles can improve the accuracy of dietary assessment [47].

In the Malaysian context, a six-month randomised controlled trial assigned 77 women post-GDM to either a low-glycaemic index (LGI) diet or a conventional healthy dietary recommendation [48]. The study reported that women in the LGI diet group lost significantly more weight and improved 2 h postprandial glucose levels. A few limitations of the use of the 3-day food record were underreporting by the subjects and the inability to capture the subjects’ habitual dietary patterns [48]. Hence, we propose the combination of a traditional dietary assessment together with a metabolomics approach to produce a more objective dietary assessment method. Additionally, dietary patterns of Malaysians may be different from those of the Caucasian population [10] and warrant further investigation in relation to T2D risk in this population.

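### The 80% power in Section 2.3 holds only if enough women turn out to have newly detected T2D, and the described design does not secure that number

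*Protocol article*

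**What the plan says.** **Size.** Section 2.3 uses a mean-difference formula with inputs from a Swedish study of women after GDM: "considering a 95% confidence level and 80% power, a total of 99 subjects will be needed for the study". A 20% allowance for non-response brings this to a minimum of 126. The article gives no number per group, difference, SD or outcome variable for the calculation.

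**Eligibility.** The same section excludes women with "previously diagnosed medical problems (such as type 1 or type 2 diabetes, cancer, and liver or renal disorders". T2D cases in the study should therefore be newly detected ones.

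**Selection.** Section 2.4: "Subjects will then be selected using systematic random sampling". No stratum or quota by glycaemic status is mentioned.

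**Classification.** Section 2.5.1: "Subjects will be grouped into either NGT, prediabetes or T2D based on their OGTT and HbA1c results". Both tests are part of the study visit, so group membership is known only after enrolment.

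**Use of the groups.** Section 2.1 makes nutritype signatures associated with T2D the primary outcome and compares three groups. Section 2.5.9 separates T2D from non-T2D. Section 2.7 fits a multinomial logistic model with confounders and adds: "Subgroup analyses will also be performed, such as early versus late postpartum", with further splits by supplement use and obesity.

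**Expected T2D.** The Discussion reports that T2D prevalence in Malaysian women after GDM "ranges between 0.8% and 6 weeks to 35.5% at 15 years postpartum".

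**The concern.** A mean-difference formula fixes the size of the groups being compared. Here the investigators do not set those sizes; they depend on how many sampled women without a previous diabetes diagnosis meet the T2D criteria. The article states a power figure without a T2D yield or any step that would produce one.

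Precision for the T2D question is governed mainly by the number of T2D cases. If these are few, a null result would still be read as coming from a study with 80% power. The adjusted multinomial odds ratios, and their repeats within subgroups, would rest on a small number of events. The formula also covers one comparison of two means, which is not the multinomial model that Section 2.7 uses for T2D.

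**Working it through.** **1. The plan's own totals.** The 99 cannot be derived, because no difference or SD is given. The step to 126 can be checked:

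- 99 × 1.2 = 118.8, which misses 126.
- 99 / 0.8 = 123.75, or 124, which is close but not 126.
- 99 = 3 × 33; 33 / 0.8 = 41.25, rounded up to 42; 3 × 42 = 126, an exact match.

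Two groups of 50 also give 126, since 50 / 0.8 = 62.5, rounded up to 63, and 2 × 63 = 126. However, 2 × 50 is 100, not 99. Three equal groups fit both totals, so that split is taken as a well-supported inference.

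**2. Implied effect (assumption).** With 33 per group, two-sided 5% and 80% power:

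d = (1.96 + 0.842) × √(2/33) = 0.69.

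The article does not state sidedness; two-sided is assumed.

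**3. Power with unequal groups.** Approximately, power = Φ(d / √(1/n₁ + 1/n₂) − 1.96). For 10 T2D against 89 non-T2D, √(1/10 + 1/89) = 0.334, 0.69/0.334 = 2.07, and Φ(0.11) = 54%. The table uses the noncentral t distribution, which gives about one point less. It takes 99 women analysed (126 × 0.8 = 100.8). For the NGT column, 25 women are assumed to have prediabetes; that share is not in the article.

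| T2D cases of 99 | NGT women | Power, T2D vs NGT | Non-T2D women | Power, T2D vs non-T2D |
|---|---|---|---|---|
| 5 | 69 | 31% | 94 | 32% |
| 10 | 64 | 52% | 89 | 53% |
| 15 | 59 | 65% | 84 | 68% |
| 20 | 54 | 74% | 79 | 78% |

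**4. T2D cases needed for 80%.**

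- T2D vs non-T2D: 21 of 99 by the normal approximation, 22 by noncentral t (21 to 22%). If all 126 are analysed: 20 (16%).
- T2D vs NGT, with the remaining women split equally between NGT and prediabetes: 33 of 99 (one third). If all 126 are analysed: 25 (20%).
- T2D vs NGT, with prediabetes held at 25 women as in the table, needs fewer: for 25 vs 49, √(1/25 + 1/49) = 0.246, 0.69/0.246 = 2.81, and Φ(0.85) = 80%. The one-third figure therefore belongs to the equal-group case.

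**5. Against the article's prevalence range.** At 0.8%, 99 × 0.008 gives about 1 case and roughly 9% power. At 35.5%, 99 × 0.355 gives about 35 cases and power of 91% against non-T2D, or 81% against NGT with the rest split equally. The range therefore lies partly below and partly above the thresholds.

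**6. Women to test for 33 T2D cases.** 33/0.05 = 660; 33/0.10 = 330; 33/0.20 = 165; 33/0.355 = 93.

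**The case against.** A reader might infer that the T2D group will certainly be far smaller than planned and that 80% power is certainly not delivered. The article does not support that. It gives only two prevalence endpoints, sets no limit on time since GDM, and plans to include women at least one year postpartum, so the yield is unknown. The upper endpoint would supply enough cases. Excluding known T2D lowers the yield only if the cited prevalences include known cases, which is not stated. The remark in the Discussion about not stratifying by treatment for T2D also sits awkwardly with a T2D group made up only of newly detected women.

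The most favourable contrast, T2D versus non-T2D, is the one used to build the nutritype models in Section 2.5.9. It needs about 21 or 22 cases, not 33.

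The per-group size and d = 0.69 are inferred. In addition, 126 is a minimum, this is a condensed article, its workflow figure is not shown, and a quota may exist in the full protocol.

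Nor is there an arithmetic error to allege: 126 reproduces exactly.

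These points limit the claim without removing it. A specific power figure is stated without its condition, and the recruitment steps that are described do not meet that condition by design.

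**Conclusion.** The point holds in conditional form. The 80% in Section 2.3 is valid only if newly detected T2D reaches about 21 to 22% of 99 women (about 16% of 126) for T2D versus non-T2D, or about one third of 99 for T2D versus NGT in equal groups. No step visible in the article secures either share. At 5 to 15% T2D, power in 99 women is about 32 to 68% and 31 to 65% respectively.

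These figures rest on an inferred 33 per group, the d of about 0.69 that follows from it, a two-sided 5% test and, for the NGT power figures, prediabetes at 25%. A different true effect would shift every value.

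It would go too far to conclude that the T2D question should be replaced by a continuous glycaemic outcome as the primary analysis. That would change the study's stated aim after recruitment began in March 2021. The article also gives no effect size on which to claim better power for such an outcome.

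**What to change.** **Restate the sample-size paragraph in Section 2.3.** Tie the 80% to one two-group mean comparison with 33 women per group, and state the difference, SD and variable used (if the split was not 33 per group, state the actual one). Give the expected share of newly detected T2D, or the share seen so far in recruitment. Report the power at that share for T2D versus NGT and for T2D versus non-T2D. If the full protocol has a quota or fills each group to a target, say so here; that would answer the point.

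**Optional.** Add supporting models of the fasting glucose, 2 h glucose and HbA1c values already measured, or of the ordered NGT, prediabetes and T2D outcome. These use every woman and leave the T2D question in place. Label the subgroup analyses exploratory.

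**Cost.** Wording and a short recalculation, plus supporting models on data already being collected. No extra participants or measurements are needed. The drawback is that the stated power is likely to look less favourable.

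### The figures 99, 20% and 126 do not reconcile as worded, and the equal groups of 33 that best explain them are not secured by the sampling described, so 80% power for a T2D comparison is conditional on the T2D share

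*Protocol article*

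**What the plan says.** Section 2.3 of the protocol article bases the sample size on a formula and on a source study: "The sample size will be estimated using the mean difference formula [20", with inputs from a Swedish study of women after GDM. It then says "considering a 95% confidence level and 80% power, a total of 99 subjects will be needed for the study", and, to cover nonresponse or refusal, "an additional 20% of subjects will be required, leading to a minimum of 126 subjects". No number per group, powered contrast, difference or SD is given.

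The same section excludes women with previously diagnosed T2D. Section 2.4 describes the selection: "Subjects will then be selected using systematic random sampling". Section 2.5.1 assigns the groups from tests done within the study: "Subjects will be grouped into either NGT, prediabetes or T2D based on their OGTT and HbA1c results".

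Section 2.1 makes the primary outcome the nutritype signatures associated with T2D. Section 2.5.9 uses a T2D against non-T2D separation, and section 2.7 compares the three groups and models T2D by multinomial logistic regression. The Discussion says that T2D prevalence in Malaysian women after GDM "ranges between 0.8% and 6 weeks to 35.5% at 15 years postpartum", which I read as 0.8% at 6 weeks and 35.5% at 15 years.

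**The concern.** There are two linked problems.

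The first is arithmetic. The stated inflation does not lead from 99 to 126, so a reader cannot tell which rule was used or which of the three figures is firm.

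The second is allocation. The simplest derivation that gives 126 exactly treats the study as three equal groups. The sampling described lets group sizes fall where prevalence puts them, and with known T2D excluded the T2D group can contain only newly detected cases. In any comparison with T2D, the smaller group largely sets the power. If few women turn out to have T2D, the stated 80% would not describe that comparison, and a null T2D result could be taken as adequately powered when it was not.

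**Working it through.** **Step 1: reproduce 126.** Inputs from section 2.3: 99 and 20%. Number of groups from section 2.1: 3.

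| Rule | Result |
|---|---|
| 99 × 1.2 | 118.8 → 119 |
| 3 × (33 × 1.2 = 39.6 → 40) | 120 |
| 99 / 0.8 | 123.75 → 124 |
| 3 × (33 / 0.8 = 41.25 → 42) | **126** |
| 105 × 1.2 (105 = 3 × 35) | 126, but from 105, not 99 |

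The ratio 126/99 is 1.273. The equal-group rule starts from 99 and is exact. Some unequal three-way splits also round up to 126: 29/33/37 gives 37 + 42 + 47 = 126. No two-way split of 99 does.

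**Step 2: the difference implied by 33 per group.** The 99 itself cannot be rebuilt, because the difference and SD are not stated. Assuming a two-sided 5% level (the sidedness is not stated) and 80% power, the normal approximation gives d = (1.960 + 0.842) × √(2/33) = 0.69. The two-sample t-test gives 0.70. This value is back-calculated and is not a figure from the plan.

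**Step 3: how large the T2D group must be.** For groups of n₁ and n₂, power at fixed d depends essentially on n₁n₂/(n₁ + n₂). At 33 v 33 this is 33 × 33/66 = 16.5, so 80% power needs at least 16.5. The smallest T2D group that meets this is:

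| Comparator | 99 analysed | 126 analysed |
|---|---|---|
| All non-T2D | 21 (21%) | 20 (16%) |
| NGT, rest split 2:1 NGT:prediabetes | 25 (25%) | 22 (17%) |
| NGT, rest split equally | 33 (33%) | 25 (20%) |

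Example: 21 × 78/99 = 16.55 suffices, while 20 × 79/99 = 15.96 does not. Both totals are shown because the 20% is for nonresponse or refusal, while the Abstract has the study involving at least 126 women.

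**Step 4: power at lower T2D shares.** Two-sample t-test, two-sided 5%, d = 0.70. The T2D shares and the 70% NGT share of the remaining women are my assumptions.

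| T2D share | 99 analysed: T2D v NGT | Power | Detectable d at 80% | Power v all non-T2D | 126 analysed: T2D v NGT | Power |
|---|---|---|---|---|---|---|
| 5% | 5 v 66 | 32% | 1.32 | 33% | 6 v 84 | 37% |
| 10% | 10 v 62 | 53% | 0.97 | 55% | 13 v 79 | 64% |
| 15% | 15 v 59 | 67% | 0.82 | 70% | 19 v 75 | 77% |
| 20% | 20 v 55 | 75% | 0.74 | 79% | 25 v 71 | 85% |
| 25% | 25 v 52 | 81% | 0.69 | 85% | not shown | not shown |

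At the bottom of the article's own prevalence range, 0.8% of 99 is about one woman, and power is about 10%.

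**The case against.** Several objections have force.

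- **Equal groups are an inference.** A reader might infer that 126 can arise only from three equal groups. It cannot be put that strongly: 29/33/37 and 105 × 1.2 also give 126, and 124 is close. The slip could lie in the 99 rather than in the 20%.
- **There is no single threshold.** A reader might conclude that a quarter of the women must have T2D. That is one scenario: 99 analysed, T2D against NGT, and about two NGT women for each woman with prediabetes. With 126 analysed, or with all non-T2D women as the comparator (the contrast used in section 2.5.9), the requirement is lower.
- **The powered contrast is not named.** Section 2.3 does not say that the 80% belongs to a T2D comparison, and its account of the source study ("Based on a study that compared dietary intake and metabolomic profile in NGT, prediabetes and metabolomic profile in women post-GDM in Gothenburg, Sweden") does not mention T2D. If the formula was applied to NGT against prediabetes, the T2D figures above do not describe it. The t-test is also a stand-in for the multinomial model in section 2.7.
- **A group target may exist elsewhere.** Figure 1, the research workflow, is not shown, and neither is the full protocol. The 126 is also a minimum, so further recruitment is not ruled out.
- **The prevalence evidence is thin.** The Discussion gives only the two ends of a range, and eligibility sets no limit on time since GDM.

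These points limit the claim to a conditional one. They do not make 99 plus 20% equal 126, and they do not supply group sizes under which the stated power holds.

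**Conclusion.** The concern holds in a limited form. As worded, 99, 20% and 126 are inconsistent: the two usual readings on the total give 119 and 124. Three groups of 33 inflated to 42 is the most natural explanation, but not a proven one. The text shown does not secure such groups.

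If the 80% is intended for T2D comparisons at 33 per group, it requires a T2D share of at least about 21–33% of 99 analysed women, or 16–20% of 126. Below that it falls quickly, to about 53% at a 10% share in the 99-woman T2D against NGT scenario. This rests on a back-calculated difference of about 0.70, a two-sided 5% level, no multiplicity adjustment, and assumed T2D and prediabetes shares.

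A reader might go further and infer that the study is underpowered, or that it has no group quota. The documents do not support either: the achieved T2D share is unknown, the powered contrast is not stated, and the workflow figure is not shown.

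**What to change.** In section 2.3:

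1. Reconcile 99, 20% and 126, and state the inflation rule actually used. If it was division by 0.8 within each group, say so. If the 99 is a misprint, correct it. Say whether 126 counts women approached or women enrolled.
2. State the number per group, the contrast that was powered, and the difference and SD taken from the source study that lead to 99. If the workflow or the full protocol sets a group target, cite it here.
3. State that the 80% is conditional on those group sizes, and give power, or the detectable T2D difference, over a plausible range of T2D shares. The tables above show the format, but they should be rerun with the real difference and SD rather than the back-calculated 0.70.
4. Commit to reporting the detectable difference at the achieved group sizes with the results.

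The cost is a change of wording and a short calculation. No extra women are needed. The stated power for T2D comparisons may become less favourable.
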